### Study population, sample size, and power analysis

2.3

The data provided by the three health insurers Sanitas, CSS, and Helsana, comprise information on a total of 8422 primary care physicians in Switzerland. These primary care physicians treated at least one patient covered by one of the three health insurances. Due to the usual administrative processing delay of claims data of 6 months by health insurers, the definitive sample size calculation had to be based on claims data from January to December 2016. In this pre-randomization claims data set, we identified 3646 eligible GPs corresponding to the inclusion criteria, as mentioned above. A random sample of 220 physicians from the Basel area was left aside for a different interventional trial. The remaining study population of 3426 physicians were randomized to the intervention or control groups, with 1713 physicians in each arm.

We conducted a power analysis that was based on a trial simulation from 50 bootstrap samples. These bootstrap samples were extracted from the pool of physicians from the database of the year 2016, which was used to select and randomize GPs. The clinically relevant effect that the study aims to detect is, on average 5% expected reduction in prescription rates. Therefore, we simulated a trial for each bootstrap sample and we applied the effect which we expected to observe in the treatment arm. To also account for any variability, we simulated effects from distribution of potential effects, which were "centered" around 5%, for every physician. The standard deviation of the prescription rate in the target population was evaluated based on the data from the year 2016, which was 0.059 on the raw scale and 0.438 on the log scale. Also, we scaled the distribution to account for the expected proportion of non-responders of 15%. For each sample, we then tested the difference using a Mann Whitney *U* test (Wilcoxon rank-sum). Hence, we evaluated the power for each bootstrap sample, and derived medians and confidence intervals from the empirical distribution, which gave an estimated median power of 0.93 (95% CI: 0.90 to 0.96).

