### Intervention and control

2.5

The first mailing was sent on December 22, 2017 and was followed by seven additional quarterly mailings, with the last mailing sent in late September 2019 (see the timeline in Fig. 1). With the first mailing, all GPs in the intervention group received (1) an accompanying letter explaining the intervention, assuring the full pseudonymization of feedback data, (2) a personalized feedback of antibiotic prescribing; (3) a response card for physicians wishing to opt-out; and (4) evidence-based guidelines on antibiotic prescribing for respiratory and urinary tract infections (see details below). No information on the study design or comparative study purpose was provided.

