### Evidence-based guidelines

2.7

Evidence-based guidelines for the management of upper and lower respiratory tract and urinary tract infections were provided once with the first mailing to the GPs in the intervention arm. We updated our guidelines from our previous pilot-RCT [12,21] with systematic literature research for additional evidence on the effectiveness of antibiotics for the treatment of these conditions for the time period of 2013 until June 2017. Also, we evaluated the literature on the effectiveness of relevant diagnostic tests for the identification of bacterial-related upper and lower respiratory tract infections in primary care. The guidelines for upper respiratory tract infections were updated together with an expert group by the Swiss Society of Infectious Diseases that is responsible for the development of Swiss national guidelines for the treatment of upper respiratory and urinary tract infections. The guidelines were provided as a paper brochure with the first mailing at the end of December 2017 to all physicians in the intervention group.

Because more than 90% of physicians' offices are located in the German- and French-speaking regions of Switzerland, we provided all information in these two official languages. We assumed that most physicians in the Swiss Italian part know either French or German, since the Swiss educational system includes German or French, and as there is not yet a medical school in the Swiss Italian part of Switzerland.

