### Outcomes

2.8

The primary outcome is the overall antibiotic use, defined as prescribed antibiotics per 100 patient consultations in the second year of intervention lasting from month 13 to month 24 (long-term intervention effect).

The secondary outcomes are (1) overall antibiotic use defined as prescribed antibiotics per 100 patient consultations from month 1–12 (first year of intervention, shorter-term intervention effect); (2) overall antibiotic use defined as prescribed antibiotics per 100 patient consultations over the entire intervention period from month 1 to month 24, with two repeated measurements, over the first and the second 12 month period of intervention; (3) use of broad-spectrum antibiotics (quinolones and oral cephalosporines) per 100 patient consultations; (4) hospitalizations rates (all-cause and related to infections based on Diagnosis Related Groups (DRG) definition); (5) Antibiotic use (prescribed antibiotics per 100 patient consultations) in five specific age groups, in patients 0–14 years, 15–24 years, 25–54 years, 55–64 years, and ≥65 years; and (6) secondary outcomes (3) to (5) will be evaluated separately over the second and first 12 months (from month 13 to month 24 and 1–12 months).

All cause hospitalization will be defined as any hospitalization (DRG-based) within 30 days after a preceeding GP consulation. Infection-related hospitalization will be defined as any hospitalization within 30 days after a preceeding GP consulation with DRG-codes for community acquired pneumonia, urinary sepsis, or sepsis. Reconsultation will be defined as any consultation within 30 days after a first GP consultation or any emergency consultation in a hospital.

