### Data analysis

2.11

Statistical analysis will be performed by the trial statistician using R (R Core Team 2017 [20]). All analyses will be conducted using the final dataset, which will be available in September 2020 (see also timeline in Fig. 1C) and will follow CONSORT guidelines and intention-to-treat principles [[22], [23], [24]]. A flowchart will describe the inclusion and follow-up of GPs by study arm. Baseline characteristics will be described by study arm with summary statistics such as median and interquartile range or number and percentage; no formal testing between arms will be performed [25]. Outcomes will be described by arm using summary statistics.

The primary outcome, the proportion of individuals with an antibiotic prescription in the second year of the intervention, will be assessed by ANCOVA modeling, with the outcome as a response, intervention (yes/no) as a factor of interest, and baseline year antibiotic prescription rate as a covariate (the baseline year is January–December 2017). Other baseline covariates of interest include comorbidities (based on pharmacy cost groups) patients' age, annual patient volume (total number of consultations per GP), and seasonality. For the primary outcome analysis, the coefficient estimates and their 95% CI will be reported. Secondary outcomes will be evaluated in the same way.

Effects for the period month 1 to month 24 will be modeled using a linear mixed model including the intervention (yes/no), time (baseline, first year, second year), an interaction term for the intervention with time, and by treating physician as random effects. Mean percentage changes from baseline will be derived for the intervention and control groups. Other baseline covariates of interest will be included as for the primary analysis.

The rates of hospitalizations and reconsultations will be modeled using logistic regressions including the intervention as a factor of interest and other relevant covariates. Hospitalization rates in the intervention and control group, with exact 95% CIs will be reported, and odds ratios for the intervention arm vs. control will be derived from the coefficients estimated for the logistic regression model.

The analysis in specific age groups will be similar to the primary analysis over the respective periods and stratified by age groups i) 0–14 years, ii) 15–24 years, iii) 25–54 years, iv) 55–64 years, and v) 65 years and over.

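### The 2017 baseline year includes up to ten days after the first mailing was posted, so the adjustment covariate is not strictly pre-intervention; the effect on the estimate is very small and towards no effect

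*Protocol article*

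**What the plan says.** Section 2.11 (Data analysis) of the protocol article specifies an ANCOVA for the primary outcome, with "baseline year antibiotic prescription rate as a covariate (the baseline year is January–December 2017". The model for months 1 to 24 in the same section uses "time (baseline, first year, second year), an interaction term for the intervention with time", and mean percentage changes from baseline are to be derived for each arm. No second definition of baseline is given for these analyses.

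Section 2.5 (Intervention and control) gives the start of the intervention: "The first mailing was sent on December 22, 2017 and was followed by seven additional quarterly mailings". That mailing was not just an announcement. Besides the accompanying letter it contained "2) a personalized feedback of antibiotic prescribing; (3) a response card for physicians wishing to opt-out; and (4) evidence-based guidelines on antibiotic prescribing". Section 2.7 (Evidence-based guidelines) confirms the timing: "The guidelines were provided as a paper brochure with the first mailing at the end of December 2017 to all physicians in the intervention group". According to the abstract, the control arm received neither guidelines nor feedback.

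Section 2.8 (Outcomes) places the primary outcome "in the second year of intervention lasting from month 13 to month 24 (long-term intervention effect"). The text does not give the calendar date on which month 1 begins. Fig. 1, which sets out the baseline and outcome periods, is not available here.

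**The concern.** A covariate used for adjustment should be measured before the treatment can act on it. Here the baseline window closes on 31 December 2017, nine days after the posting date, and only one arm received anything. If GPs in the intervention arm cut their prescribing at once, their measured baseline falls slightly. The ANCOVA then predicts a lower second-year rate for that arm and credits the difference to baseline instead of to the intervention. Percentage changes from baseline in the intervention arm would be understated in the same way.

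This is not a detail left for an analysis plan. The article prints both dates, and they overlap. The text shown has no run-in rule and no exclusion of the last days of December. If month 1 begins on 1 January 2018, those days count as baseline only. If it begins at posting, they count in both the baseline and the first year.

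**Working it through.** **Inputs from the protocol article**
- Baseline: 1 January to 31 December 2017, 365 days (section 2.11).
- First mailing posted: 22 December 2017 (section 2.5).
- Target effect (section 2.3): "The clinically relevant effect that the study aims to detect is, on average 5% expected reduction in prescription rates".
- SD of the prescription rate (section 2.3), "which was 0.059 on the raw scale and 0.438 on the log scale".
- 1713 GPs per arm; stated median power 0.93 (section 2.3).

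**Assumptions not in the article**
- Two-sided alpha of 0.05, and analysis on the log scale.
- ANCOVA slope of 0.6 to 1.0.
- For the upper bound only: the full 5% response in force from the day of posting, and late-December consultations and prescribing at the annual average.

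**Step 1. Reproduce the plan's power.**
Log effect = −ln(0.95) = 0.0513.
Unadjusted SE = 0.438 × √(2/1713) = 0.0150.
Power = Φ(0.0513/0.0150 − 1.96) = 0.929, or 0.918 with the Mann-Whitney efficiency factor 3/π applied to n. Both agree with 0.93. This takes 5% as the average effect after the 15% non-response. Reducing it further to 4.25% gives 0.83 and does not reproduce the figure.

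**Step 2. Overlap.**
22 to 31 December inclusive is 10 days; 10/365 = 2.7%.

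**Step 3. Upper bound on the baseline shift.**
−ln(1 − 0.05 × 10/365) = 0.00137, so the intervention-arm baseline is lowered by about 0.14%.

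**Step 4. Effect on the adjusted estimate.**
Attenuation = slope × 0.00137. The estimated reduction is 1 − exp(−(0.0513 − attenuation)).

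| Slope | Attenuation (log scale × 100) | Share of effect | Estimated reduction (true 5.00%) | In unadjusted SEs |
|---|---|---|---|---|
| 0.6 | 0.08 | 1.6% | 4.92% | 0.05 |
| 0.8 | 0.11 | 2.1% | 4.90% | 0.07 |
| 1.0 | 0.14 | 2.7% | 4.87% | 0.09 |

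At slope 1.0, power falls from 0.929 to 0.916. The ANCOVA's own SE will be smaller than the unadjusted one. If the SD is the same in both years, the slope equals the correlation. A slope of 0.8 then gives SE = 0.0150 × √(1 − 0.64) = 0.0090 and a ratio of 0.0011/0.0090 = 0.12, which is still small.

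**Step 5. Sensitivity to the assumptions.**
- *Fewer exposed days.* 22 December 2017 was a Friday. 23–24 and 30–31 December were weekends and 25 December was Christmas, which leaves 26–29 December: four weekdays at most. With about 250 working days a year (assumed), the shift is 0.05 × 4/250 = 0.0008. Attenuation is then 0.05 to 0.08 percentage points for slopes 0.6 to 1.0.
- *Higher density.* If prescribing in those ten days were twice the annual average, the shift would be 0.27%, the estimate 4.74% at slope 1.0 and power 0.900.

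**The case against.** The strongest reply is that posting is not exposure. The letter went by post on the Friday before Christmas, and a GP had perhaps three or four ordinary weekdays in which to receive it, read it and change practice. An immediate full response is also unlikely. The 5% is the average effect the trial aims to detect, and the primary objective is the long-term effect in the second year. The group's earlier trial of quarterly feedback, described in the Background, found no overall reduction in its first year (difference 0.8%, 95% CI −2.6% to 4.3%, measured in defined daily doses). Finally, the outcome is a rate per 100 consultations, so the share that matters is of consultations, not of calendar days. The article gives no late-December figure for it.

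All of this stands, and it is why the size above is a ceiling. It does not remove the overlap between two dates that the article itself prints.

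A reader might go further and infer that ten days of actual exposure were recorded as baseline, or that the trial's result is materially distorted. The documents support neither. They give a posting date, not a date of receipt or response. The outcome window of months 13 to 24 lies well clear of the overlap. If the intervention has no effect, there is no shift at all, so the overlap cannot produce a false benefit.

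**Conclusion.** The point holds as a minor inconsistency of definition. As written, the ANCOVA covariate includes up to 10 days (at most 2.7% of the year) after the intervention was posted to one arm. The extension to the mixed model and the percentage changes is a natural reading, because no other baseline is defined, but the text does not say so outright.

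Under the upper-bound assumptions the attenuation is 0.08 to 0.14 percentage points of a 5% effect, under 0.1 unadjusted SE, with a loss of about one point of power. The true figure is probably lower. Only a late-December prescribing density well above average would raise it; at double density the loss is about 0.26 percentage points. The direction is towards no effect throughout, provided that any early response is a reduction in prescribing. Whether the ten days also count in the first year cannot be settled from the text without Fig. 1.

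**What to change.** Define the baseline period as 1 January to 21 December 2017 in both arms. Use that one window for the ANCOVA covariate, the baseline level of the mixed model and the percentage changes. State the calendar date on which month 1 begins, not before 22 December 2017, so that no day counts twice.

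Table 1 lists dates of consultation and of prescription, so this needs only a date filter and one line of wording. It costs 10 of 365 baseline days and leaves late December slightly under-represented compared with the outcome years. Because the outcome is a rate per consultation and the truncation is identical in both arms, the mismatch may touch the within-arm percentage changes slightly but does not favour either arm.

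A full twelve months from 1 December 2016 to 30 November 2017 would cover each season once, but it is less attractive. It brings in a month of the 2016 data on which GPs were selected as top-75% prescribers (sections 2.2 and 2.3), which could add some regression to the mean to the within-arm changes. It also discards three unaffected weeks of December 2017.

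### The month 1 to 24 mixed model treats the 2017 baseline as a response with a free arm difference and uses one physician random intercept: unbiased, but less precise than the trial's own ANCOVA, and with unreliable standard errors if correlation decays over time

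*Protocol article*

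**What the plan says.** All references are to the protocol article.

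- **Outcomes**, secondary outcome (2): the antibiotic prescription rate, assessed "over the entire intervention period from month 1 to month 24, with two repeated measurements, over the first and the second 12 month period".
- **Data analysis**, model for this outcome: a linear mixed model that has an arm term and, besides it, "time (baseline, first year, second year), an interaction term for the intervention with time, and by treating physician as random effects". The further covariates are those of the primary analysis, and the stated output is: "Mean percentage changes from baseline will be derived for the intervention and control groups".
- **Data analysis**, primary outcome: ANCOVA with "baseline year antibiotic prescription rate as a covariate (the baseline year is January–December 2017"). The same paragraph says that secondary outcomes are handled likewise, before the mixed model is introduced for months 1 to 24.
- **Intervention and control**: "The first mailing was sent on December 22, 2017". Apart from its last ten days, 2017 therefore lies before any contact with the GPs.

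The article does not say that the arms share a baseline mean in the mixed model. It names no covariance structure beyond the physician random effect.

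**The concern.** When baseline is one level of the time factor and the intervention main effect is unconstrained, that main effect (with baseline as reference) absorbs the chance difference between the arms in 2017. Each intervention-by-time coefficient is then the arm difference in that year minus the arm difference in 2017. Subtracting the whole baseline difference, rather than the fraction of it that predicts the later year, adds noise. Randomisation makes the expected 2017 means equal, so nothing is gained in return. The primary ANCOVA avoids this loss; the 24-month model does not.

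A second issue comes with the random effect. On its plain reading it is a random intercept per physician, which makes the correlation between 2017 and year 2 equal to that between adjacent years. Prescribing rates two years apart may well be less alike. The model would then misstate the variance of its own contrasts, and a large sample does not cure that.

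At stake are the width and the coverage of the confidence intervals for one secondary outcome. The primary analysis is not affected.

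**Working it through.** **Inputs from the article (Study population, sample size, and power analysis):** 1713 GPs per arm; log-scale SD 0.438; target mean reduction 5%, a log difference of −ln(0.95) = 0.0513; stated median power 0.93.

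**Assumed, because the article does not give them:** two-sided alpha 0.05; equal variance in each year; between-year correlation ρ, shown over a range.

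**1. The plan's own figure.** The SE of an unadjusted single-year comparison is 0.438 × √(2/1713) = 0.01497. Power = Φ(0.0513/0.01497 − 1.96) = 0.929. With the Mann-Whitney efficiency factor 3/π it is 0.918. Both agree with the stated 0.93, so these inputs are a fair basis.

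**2. Variance of each contrast**, in units of the unadjusted single-year variance, with equal correlation ρ between all years:

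- Year 2, difference in change: 2(1 − ρ). Baseline-adjusted: 1 − ρ². Ratio: 2/(1 + ρ).
- Mean of years 1 and 2, difference in change: 1.5(1 − ρ). Baseline-adjusted: (1 + ρ)/2 − ρ² = (1 − ρ)(1 + 2ρ)/2. Ratio: 3/(1 + 2ρ).

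Both ratios exceed 1 for every ρ below 1.

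| ρ (assumed) | Year-2 variance ratio | 24-month variance ratio | 24-month SE, planned vs adjusted | Interval width ratio, 24-month |
|---|---|---|---|---|
| 0.5 | 1.33 | 1.50 | 0.01296 vs 0.01058 | 1.22 |
| 0.7 | 1.18 | 1.25 | 0.01004 vs 0.00898 | 1.12 |
| 0.8 | 1.11 | 1.15 | 0.00820 vs 0.00763 | 1.07 |
| 0.9 | 1.05 | 1.07 | 0.00580 vs 0.00560 | 1.04 |

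**3. Power for a 5% reduction, 24-month mean.** At ρ = 0.5: Φ(0.0513/0.01296 − 1.96) = 0.977 as planned, against Φ(0.0513/0.01058 − 1.96) = 0.998 adjusted. At ρ = 0.7 or more, both exceed 0.999.

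**4. Check by simulation at ρ = 0.8.** In one fitted data set the year-2 interaction equalled the raw difference in mean changes (−0.04608 for both), with model SE 0.00946. The model with a common baseline mean gave SE 0.00897 and an estimate (−0.04162) close to ANCOVA (−0.04188). Over 2000 trials, the year-2 difference in change and the ANCOVA were both unbiased (means −0.0515 and −0.0514; truth −0.0513). The variance ratios were 1.10 for year 2 and 1.13 for the 24-month mean, against 1.11 and 1.15 in theory.

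**5. Decaying correlation (illustration).** Assume 0.8 between adjacent years and 0.64 between 2017 and year 2. A random-intercept model fits one common value, (0.8 + 0.8 + 0.64)/3 = 0.747.

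- Year 2: true variance 2(1 − 0.64) = 0.72; modelled 2(1 − 0.747) = 0.507. The SE is too small by the factor √(0.507/0.72) = 0.84, and the type I error is 2Φ(−1.96 × 0.84) = 10%.
- 24-month mean: true variance 1 + (1 + 0.8)/2 − (0.8 + 0.64) = 0.46; modelled 1.5(1 − 0.747) = 0.38. The factor is 0.91 and the type I error 7.5%.
- Year 1 errs the other way: true 2(1 − 0.8) = 0.40, modelled 0.507, so its SE is too large.

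A simulation of 4000 null trials under these correlations gave 10.2% for year 2 and 7.5% for the 24-month mean.

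**The case against.** The strongest reply is that nothing here is an error. The planned estimator is unbiased, it serves one secondary outcome, and the primary outcome already has ANCOVA. At 1713 GPs per arm the power cost is slight, and for ρ above 1/3 the planned 24-month contrast is still more precise than the unadjusted single-year comparison on which the trial was powered, since 1.5(1 − ρ) is then below 1. All of this stands, and it is why the point is minor.

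Three stronger readings are tempting, but the article does not support them.

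- **That the model yields no 24-month effect.** It gives two yearly interaction coefficients, and their average is an ordinary linear contrast; in the fitted example it was −0.0441 with SE 0.0082. A condensed article may leave the naming of that contrast to the full protocol or the analysis plan.
- **That Outcomes and Data analysis contradict each other**, because one has "with two repeated measurements, over the first and the second 12 month period of intervention" and the other three time levels. The first can be read as counting measurements within the intervention period, and the second as adding the reference level needed for change from baseline. Both can be true.
- **That the trial will publish rival year-2 results.** The two methods would give different numbers, but the article assigns the year-2 effect to ANCOVA and uses the mixed model for the whole period.

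One caution on terms: 2017 is best called the baseline year. The article applies its pre-randomisation label to the 2016 data ("In this pre-randomization claims data set, we identified 3646 eligible GPs") and gives no date of randomisation. The algebra is unchanged.

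The reply about efficiency does not answer the covariance issue, which concerns valid standard errors and does not shrink with sample size.

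**Conclusion.** The concern holds as a minor one. As written, the 24-month model estimates differences in change from 2017, which is unbiased but less precise than the baseline adjustment that the trial uses for its primary outcome. The excess variance is 50%, 25% or 7% for the 24-month mean, and 33%, 18% or 5% for year 2, at ρ = 0.5, 0.7 or 0.9. These figures rest on equal variances and equal correlation, with a ρ that the article does not give; the direction holds for any ρ below 1 under that structure. The practical cost is wider intervals, 4% to 22% for the 24-month mean over that range, with little loss of power.

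The random-intercept structure adds a conditional risk. If correlation falls with time, the standard errors for year 2 and the 24-month mean will be too small. The 10% and 7.5% error rates illustrate one assumed pattern and do not predict this trial's data.

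**What to change.** 1. Keep baseline, year 1 and year 2 as responses, but constrain the two arms to a common 2017 mean by omitting the intervention main effect and keeping the arm terms for years 1 and 2. The planned percentage changes from baseline remain available from the model.
2. Alternatively, use years 1 and 2 as the only responses, with the 2017 rate as a covariate whose slope may differ by year. The percentage changes from baseline must then be derived separately.
3. In either case use an unstructured within-GP covariance in place of the single random intercept.
4. Report the average of the year-1 and year-2 between-arm contrasts, with its 95% CI, as the 24-month effect.

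The cost is slightly more model specification. No new data are needed, and with at most three measurements per GP and 3426 GPs, an unstructured covariance should be easy to estimate.

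### The mixed model for the month 1–24 secondary outcome, read plainly, assumes equal variances and equal correlation between all three years; if correlation falls with distance, the two-year interval is too narrow

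*Protocol article*

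**What the plan says.** Section 2.8 (Outcomes) of the protocol article defines secondary outcome (2) as antibiotic use "over the entire intervention period from month 1 to month 24, with two repeated measurements". Section 2.11 (Data analysis) assigns the model: "Effects for the period month 1 to month 24 will be modeled using a linear mixed model". Its fixed part has arm, time and their interaction. Time has three levels: baseline, first year and second year. The random part is given in the words "an interaction term for the intervention with time, and by treating physician as random effects". Baseline covariates are added as for the primary analysis, and mean percentage changes from baseline are to be derived for each arm. Section 2.11 also states that "the baseline year is January–December 2017", so year 1 lies one year from baseline and year 2 lies two years from it.

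The primary second-year outcome is handled separately: it "will be assessed by ANCOVA modeling, with the outcome as a response, intervention (yes/no) as a factor of interest", with the baseline rate as covariate. The section then adds: "Secondary outcomes will be evaluated in the same way".

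**The concern.** With one value per physician per year, a physician random effect is a random intercept. The model then has one between-physician variance and one residual variance. It treats the 2017–2019 correlation as equal to the 2017–2018 and 2018–2019 correlations, and the three years as equally variable. If individual physicians' rates move gradually, years further apart correlate less. The pooled residual variance is then too small for a change over two years and too large for a change over one year.

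With complete data, the estimated arm differences in change stay unbiased; the error is in their standard errors. At stake is the interval for the 24-month effect, a named secondary outcome. A large sample does not help, because the ratio of the reported to the correct standard error does not depend on the number of physicians.

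**Working it through.** **The plan's own figure.** Section 2.3 reports median power of 0.93 with 1713 physicians per arm, a 5% mean reduction and a log-scale SD of 0.438. The difference is −ln(0.95) = 0.0513 and its standard error is 0.438 × √(2/1713) = 0.01497. At two-sided 5% (assumed, as alpha is not stated), power = Φ(0.0513/0.01497 − 1.96) = 0.929. This agrees with the plan. It does not involve the mixed model, so the present point leaves it unchanged.

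**Inputs for the mixed model.** The three time levels, the physician random effect, 1713 per arm and the SD come from the article. The between-year correlations do not. I write r1 for the correlation one year apart and r2 for that two years apart, and treat both as assumptions. I take equal variances σ² and complete data, and leave out covariates.

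**Formulas.** For a contrast c of the three annual values, the variance of the difference between arms is (2/n) × c′Vc.

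- The random-intercept model uses a residual variance of σ²(1 − r̄), where r̄ = (2r1 + r2)/3.
- Year-1 change: the model uses 2σ²(1 − r̄); the truth is 2σ²(1 − r1).
- Year-2 change: the model uses 2σ²(1 − r̄); the truth is 2σ²(1 − r2).
- Average of years 1 and 2 minus baseline: the model uses 1.5σ²(1 − r̄); the truth is σ²(1.5 − 0.5r1 − r2).
- SE ratio = √(model/true). True size = 2 × [1 − Φ(1.96 × ratio)].

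**Example, r1/r2 = 0.85/0.75.** r̄ = 0.8167, so 1 − r̄ = 0.1833.

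- Year 2: √(0.1833/0.25) = 0.856, size 9.3%.
- Year 1: √(0.1833/0.15) = 1.106, so the interval is 11% too wide.
- Two-year average: √(0.275/0.325) = 0.920, size 7.1%.

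**Range.**

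| Assumed r1/r2 | Two-year average: ratio, size | Year 2: ratio, size | Year 1: ratio |
|---|---|---|---|
| 0.85/0.85 | 1.00, 5.0% | 1.00, 5.0% | 1.00 |
| 0.85/0.80 | 0.953, 6.2% | 0.913, 7.4% | 1.05 |
| 0.85/0.75 | 0.920, 7.1% | 0.856, 9.3% | 1.11 |
| 0.90/0.81 | 0.901, 7.7% | 0.827, 10.5% | 1.14 |

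**Check in absolute terms.** At 0.80/0.64 with SD 0.438, the model reports a standard error of 0.01065 for both interaction terms. The correct values are 0.00947 (year 1) and 0.01270 (year 2).

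**Check by simulation.** In 4000 simulated trials per setting, coverage of the 95% intervals for year 1/year 2 was 97.6%/89.3% at 0.80/0.64, 96.2%/91.6% at 0.80/0.70 and 95.3%/94.8% at 0.80/0.80. A fitted random-intercept model on one data set generated at 0.80/0.64 returned the same standard error, 0.0108, for both interaction terms.

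**The case against.** **The article does not spell out a bare random intercept.** Covariance structure and standard-error method are often left to an analysis plan, and none is shown here. The plural in the quoted phrase could cover a random slope. This lowers certainty. But section 2.11 lists the model's fixed and random parts, and physician is the only random term in the list. The point is therefore about a stated model in its plain reading, not about a missing detail.

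**The premise is not documented.** The article gives no between-year correlation and no evidence of drift. This stands: the size cannot be derived from the document. Drift must also be specific to the physician, since a trend common to all is absorbed by the time factor. At 0.85/0.84 the year-2 test has size of only 5.5%.

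**The contrast is not named.** The only output listed from this model is mean percentage change from baseline by arm, so it is not fixed which contrast carries the 24-month conclusion. Section 2.8 also speaks of an outcome "with two repeated measurements, over the first and the second 12 month period of intervention". If baseline were a covariate and only the two intervention years were responses, there would be a single within-physician correlation and the question of unequal lags would disappear. Section 2.11, however, lists baseline as a level of time, which makes three responses the more natural reading.

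**A stronger inference is tempting.** A reader might conclude that the trial risks a false second-year finding, or would miss a first-year effect. The document does not support this. The second-year result comes from the ANCOVA, and the wording on secondary outcomes extends the same method to the first-year outcome. Neither analysis uses the three-year covariance.

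**Conclusion.** The point holds for secondary outcome (2) only. On the plain reading of section 2.11, and if the two-year-lag correlation is below the one-year-lag correlations, the interval for the two-year average against baseline is too narrow. The direction follows from the algebra. The size, about 6.2% to 7.7% for a nominal 5% test, rests on the assumed correlations 0.85/0.80 to 0.90/0.81, equal variances and complete data. Within this model, the year-2 interaction test would have size 7.4% to 10.5%, and the year-1 interval would be 5% to 14% too wide. With equal correlations the error is nil.

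The weight is modest: one secondary analysis, with a magnitude the document cannot settle. The year-specific distortions matter only if interaction terms from this model are reported beside the ANCOVA results.

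**What to change.** Fit the month 1–24 model with an unstructured within-physician covariance over the three annual values, including year-specific variances. In R this is a generalised least squares or repeated-measures mixed model. Alternatively, keep the random intercept and report physician-clustered robust standard errors. State in the same sentence which contrast represents the 24-month effect, and whether baseline is a response or a covariate.

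The cost is one line of model specification. An unstructured 3 × 3 covariance has six parameters against two for the random intercept, so four more, which is negligible with 3426 physicians. If the correlations turn out equal, nothing material is lost. The sample size, the primary analysis and the first-year analysis need no change.
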